### Sample size

In calculating the sample size, we assumed a power of 90% and α value of 5%, in order to detect a difference of 1.6 days with migraine with a standard deviation of 2.8 days; this implies a sample size of 72 per group in a design with three equal groups. We propose to recruit 270 patients in order to allow for a 20% withdrawal rate.

### Interventions

The treatment strategies with verum and with sham acupuncture were developed by means of consensus with experienced acupuncture practitioners. All the patients will be allowed to take symptomatic medication to treat headache episodes if necessary, and to continue taking the medication to prevent migraine attacks, following their GPs' recommendations and those of the Headache Study Group of the Spanish Neurological Society [34].

The two groups will receive a total of 8 acupuncture sessions (at a rate of 1 session per week), each lasting 30 minutes, comprising the technique described below and at the locations specified. The acupuncture needles will be sterile, single-use, model S-J2030, made by Seirin Corporation (Shizuoka, Japan) in accordance with EC regulations.

#### A) Verum acupuncture

Individualized treatment on the basis of diagnosis in accordance with traditional Chinese medicine (TCM), which the acupuncture physician may modify in accordance with the evolution of the patient's symptoms. The TCM diagnosis, evolution, points and techniques applied should be recorded in the DRB.

The doctors responsible for the treatment (specialists in acupuncture with a minimum training of 600 hours and a mean experience of 5.7 years) will insert sterile, single-use filiform acupuncture needles, with a length of 10–30 mm and a diameter of 0.20 mm, with the aid of a guide tube at each of the points, after first disinfecting the skin and with the patient in decubitus. The puncture will be made in accordance with the standards of TCM, to a depth of 1–3 cm, depending on the points selected. The insertion will be followed by stimulation performed with bidirectional rotation actions of the needle sheath in order to produce the sensation known as *Deqi*, commonly described as a sensation of irradiation. The needle will be maintained in place for 30 minutes, with 1–3 manipulations per session.

Any adverse reaction or side effect should be recorded in the DRB, with a detailed description, and stating the date of occurrence.

The time dedicated to the patients allocated to each of the groups should be identical. Similarly, the same time should be devoted to pre and post session evaluations.

The patients randomly selected for the SPECT diagnostic test will be given their first session at the Nuclear Medicine Department of the Virgen de las Nieves Hospital. The remaining sessions, as well as those applied to the other patients, will be performed at the healthcare centres participating in the trial.

#### B) Sham acupuncture

The patients who are randomly assigned to this group will be given minimal acupuncture (the real insertion of acupuncture needles, to a depth of less than 3 mm) at 5 bilateral non-acupuncture points located 1.5 cm from the mean dorsal line and lumbar curve, specifically, at the spinal apophysis of the T10, T11, T12, L1 and L3 vertebrae.

The technique will not differ at all from that used for Group A, except that no attempt will be made to produce the *Deqi *sensation.

#### C) Conventional treatment

The patients will be given the conventional treatment prescribed by their GP.

### Brain perfusion tomography (SPECT)

#### Preparation

▪ During the 24 hours prior to the examination, the patient must not consume coffee, colas, energy drinks, alcohol, tobacco or any drugs that might affect the cerebral blood flow.

▪ The procedure will be explained to the patient and his/her capacity to collaborate in the performance of the examination will be assessed.

#### Criteria for exclusion

Patients will be excluded from the trial if they are lactating or have a case history suggesting possible alterations to brain perfusion patterns in the SPECT test (such as cerebrovascular accident, traumatic brain injury, alcohol or drug abuse, or severe psychiatric disorders).

#### Radiopharmaceuticals

The radiopharmaceutical used will be 99mTc-ECD (Neurolite, Bristol-Myers Squibb Pharma Belgium Sprl). The manufacturer's instructions will be followed for reconstitution and labelling of the product. The dose given to each patient will be measured using an activimeter (Capintec CRC-35R, Cleveland Ohio USA) immediately following intravenous administration of the radiopharmaceutical. Its quality will be controlled in accordance with the method described by the manufacturer, to achieve at least the recommended radiochemical purity of 90%.

#### Gammacamera

In carrying out the examination, we will use a triple-head gammacamera (Picker Prism 3000, Cleveland Ohio USA), equipped with collimators for a low-energy and ultra high-resolution neuro-fan beam (Leuhr-NeuroFan), connected to a Picker Odyssey FX image processing workstation.

#### Procedure

▪ Baseline or pre-acupuncture trial:

• With the patient in decubitus, eyes open and ears un-occluded, administer 260 MBq (7 mCi) of 99mTc-ECD intravenously, with the vein canalized at least 10 minutes previously.

• Image acquisition will begin 20 minutes following the injection of the radiopharmaceutical, in accordance with the following parameters: 360° circular orbit, rotation radius of 12.9 cm, step and shoot mode (3°/40 sec/step), 128 × 128 matrix, no zoom, and an energy window of 140 ± 20 KeV. Total acquisition time, 45 minutes.

• After this initial image acquisition, the patients will be given the first acupuncture session (verum or sham), under the following procedure:

1. Group A: verum acupuncture at LI4 and LIV3 (these points were decided upon by consensus among the acupuncture physicians taking part in the trial, and because they are the ones most frequently employed in treating primary headache [35]). The insertion will be followed by stimulation performed with bidirectional rotation actions of the needle sheath in order to produce the *Deqi*. The needle will be maintained in place for 30 minutes, with 1–3 manipulations per session.

2. Group B: sham acupuncture at two bilateral points, located 1.5 cm from the spinal apophysis of the T12 and L1 vertebrae, at a depth of less than 3 mm. The technique will not differ at all from that used for Group A, except that no attempt will be made to produce the *Deqi *sensation.

▪ Post-acupuncture trial:

• 5 minutes before ending the acupuncture session, administer 925 MBq (25 mCi) of 99mTc-ECD intravenously. Image acquisition will begin approximately 30 minutes later, using the same acquisition protocol and with a total acquisition time of 20 minutes.

▪ Post-treatment trial:

• This will be performed at week 12 after randomisation.

• This trial will be carried out with the same dose of radiopharmaceuticals and under acquisition conditions identical to those of the post-acupuncture study.

#### Image processing and analysis

For image reconstruction, will be used a filtered backprojection algorithm, using Low-Pass filter Butterworth type (6.0 and a cutoff frequency of 0.3), and attenuation correction by Chang's method with an attenuation coefficient of 0.11 cm-1. After reconstruction imaging is reoriented in cross sectional planes according orbito-meatal axis (transaxial, saggital and coronal) for study comparison. Imaging will be evaluated both qualitatively and semi-quantitatively. For visual assessment, the cross-sections will be summed two by two. In the semi-quantitative analysis, they will be summed five by five.

The "Brain Ratios" program will be employed for semi-quantitative image analysis. This program enables us to plot and locate elliptical, rectangular or irregular regions of interest (ROI) in the cerebral cortex, automatically, interactively or manually. It is also possible to apply ROI that have been stored from previous studies. The location and size of the different ROI can be modified, if necessary.

In the semi-automatic method, the operator selects a transaxial image that is reoriented in the orbital-meatal plane, centred on the central grey matter, and draws an ellipse to outline the external borders of the cerebral cortex. Then, within the ellipse, the program identifies 12 regions in the right cerebral hemisphere and 12 symmetric regions in the left cerebral hemisphere.

The following regions are specified: superior, middle and inferior frontal, anterior cingulated, inferior, middle and superior temporal, posterior/precuneous cingulated, thalamus, cerebellum, occipital cortex and left and right hemispheres, as well as the whole brain. The advantage of using this method is that it is not operator dependent. The program determines the number of pixels, the total counts and the activity normalized by surface (pixel of each ROI). It also determines the indices of the total counts and of the mean number of counts per pixel among each precise ROI and another one used as reference (left and right hemisphere, cerebellum, occipital cortex). The values for the regional brain perfusion in the post-acupuncture study will be obtained by calculating the number of total counts in each ROI, and subtracting from this value the decay-adjusted total number of counts for the same ROI in the pre-acupuncture study. The mean number of counts per pixel in each ROI will be normalized to the activity of the whole brain.

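### The stated SPECT scan times contradict each other, and if the 45- and 20-minute figures hold, the dose-subtraction rule lacks a scan-time scaling and inflates regional change about 1.4-fold

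*Protocol article*

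**What the plan says.** All references are to the protocol article, under Brain perfusion tomography (SPECT) unless stated.

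- **Procedure, baseline scan.** The first injection is 260 MBq. On timing: "Image acquisition will begin 20 minutes following the injection of the radiopharmaceutical". The orbit is 360°, in "step and shoot mode (3°/40 sec/step), 128 × 128 matrix, no zoom". Then: "Total acquisition time, 45 minutes".
- **Procedure, post-acupuncture scan.** The 30-minute needling session follows the baseline scan. Five minutes before it ends, 925 MBq is injected. Imaging starts about 30 minutes later, "using the same acquisition protocol and with a total acquisition time of 20 minutes".
- **Gammacamera.** The camera is a "triple-head gammacamera".
- **Image processing and analysis.** The post-acupuncture value for each region of interest is its total count after "subtracting from this value the decay-adjusted total number of counts for the same ROI in the pre-acupuncture study". Mean counts per pixel are then normalised to the whole brain.
- **Secondary outcome measures.** Percentage change per region and an index of laterality are calculated for the semi-quantitative analysis.

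**The concern.** When the second scan is taken, tracer from the first injection is still in the brain, so its contribution has to be removed. Total counts grow with counting time as well as with activity. A residual measured over 45 minutes and carried forward by a decay factor alone is therefore too large to subtract from a 20-minute scan.

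The excess has the pre-acupuncture regional pattern. Taking out too much of that pattern pushes each normalised post-acupuncture value further from its baseline, in whichever direction it had already moved. The size of the regional change, which is the quantity the SPECT outcome reports, would then be overstated.

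Whether this happens depends on the actual counting times, and the Procedure does not give a consistent account of them.

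**Working it through.** The plan states no figure for the size of the subtraction, so there is none to reproduce.

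**1. Do the timing figures agree?**
- 360° / 3° = 120 views; 120 / 3 heads = 40 stops; 40 × 40 s = 1,600 s = 26.7 min.
- If each head covers the full circle: 120 × 40 s = 80 min.
- With 40 stops, 45 min would mean 67.5 s per stop and 20 min would mean 30 s per stop. The text states 40 s.
- Set-up time could stretch 26.7 minutes towards 45 but cannot shrink it to 20.

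Neither stated duration follows from the step settings, and one protocol cannot take both 45 and 20 minutes on the same camera.

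**2. Size if 45 and 20 minutes are the counting times**

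Inputs from the Procedure: 260 MBq at time 0; scan from 20 to 65 min; session starts at 65 min at the earliest; 925 MBq at 65 + 25 = 90 min; scan from 120 to 140 min.

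Assumptions not in the document: a 99mTc half-life of 6.01 h (λ = ln 2 / 360.6 min = 0.00192 per min), the same uptake and sensitivity for both doses, and the gap between the baseline scan and the session.

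Counts = activity × (e^(−λ·start) − e^(−λ·end)) / λ, in MBq·min. With no gap:

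- Baseline scan, 260 MBq over 20–65 min: 10,786
- Decay factor between scan midpoints (42.5 to 130 min, 87.5 min apart): e^(−λ·87.5) = 0.845
- Amount subtracted: 10,786 × 0.845 = 9,116
- True first-dose residual in the second scan, 260 MBq over 120–140 min: 4,050
- Ratio: 9,116 / 4,050 = 2.25, which is 45/20
- Second-dose counts, 925 MBq over 30–50 min after its injection: C2 = 17,132
- Excess subtracted (from unrounded values): E = 5,065, or 29.6% of C2

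Let p and q be a region's relative perfusion before and after. After whole-brain normalisation the computed post value is (q·C2 − p·E) / (C2 − E). Its difference from p is (q − p) × C2 / (C2 − E). The factor is 17,132 / (17,132 − 5,065) = 17,132 / 12,067 = **1.42**. A true 5% change reads 7.1%, and a true 10% change reads 14.2%.

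| Gap, baseline scan to session | Decay factor | E as % of C2 | Inflation |
|---|---|---|---|
| 0 min | 0.845 | 29.6 | 1.42 |
| 10 min | 0.829 | 29.0 | 1.41 |
| 30 min | 0.798 | 27.9 | 1.39 |
| 60 min | 0.753 | 26.3 | 1.36 |

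In the limit of no decay, E = 260 × (45 − 20) = 6,500, C2 = 925 × 20 = 18,500, and the factor is 18,500 / 12,000 = 1.54.

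**3. Laterality**

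With baseline asymmetry a and true post asymmetry b, the same algebra gives about b + 0.42 × (b − a) at no gap. A 10% asymmetry that fully normalises would read about −4%, an apparent reversal.

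**4. Size under the other readings**

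If both scans use the same time per step, or if the baseline counts are multiplied by 20/45 before subtraction, the factor is 1.00.

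**The case against.** The strongest objection is that the inflation rests on durations that the Procedure itself puts in doubt. If the 40-second step and the common protocol govern both scans, counting times are equal and nothing is over-subtracted. This stands, and it makes the 1.4-fold figure conditional. It does not remove the point, because the stated figures cannot all be true.

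A second objection is that an article condenses the imaging manual, which may work on count rates. That has some weight. But the article does not leave the rule open: it specifies total counts, names decay as the adjustment and gives two different durations.

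Third, the factor C2 / (C2 − E) multiplies signal and noise alike, in both arms. If timing is similar across patients, verum-versus-sham test statistics and standardised effects for percentage change hardly move. This also stands. A reader might infer that the rule favours one arm or costs precision in the comparison, and the documents do not support that.

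Fourth, a reader who guessed a decay factor of 0.90 would get 18,500 / (18,500 − 0.90 × 6,500) = 1.46. With the assumed half-life this needs scan midpoints about 55 minutes apart, and the stated schedule puts them at least 87.5 minutes apart.

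**Conclusion.** The contradiction between 45 minutes, 20 minutes and the 3°/40-second steps is certain on the text. The inflation is conditional. If 45 and 20 minutes are the true counting times, the rule removes the first dose's residual at 2.25 times its size. Whole-brain-normalised changes at the immediate post-acupuncture scan are then multiplied by about 1.42 to 1.36, given a half-life of about 6 h, equal uptake and sensitivity for the two doses, and a gap of 0 to 60 minutes. Laterality values computed from that scan are distorted as well. With equal time per step there is no inflation.

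A reader might infer that all SPECT changes in the trial are overstated by 40%. The documents do not support that: the subtraction is prescribed only for the immediate post-acupuncture scan, not for the week-12 scan. The primary outcome, days with migraine, is unaffected. What is at risk is the reported size of percentage change and laterality, secondary outcomes measured in one patient in three from the two acupuncture arms. The point merits correction but does not threaten the trial's main conclusion.

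**What to change.** Reconcile the 45-minute, 20-minute and 3°/40-second figures, and state the counting time per stop and the number of stops for each scan. Then do the subtraction on count rates. Equivalently, before normalising, compute

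post total counts − decay-adjusted pre total counts × (post duration / pre duration),

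using the durations actually recorded for each patient. With 45 and 20 minutes the multiplier is 20/45 = 0.44; with equal durations it is 1 and the rule is unchanged.

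The cost is one scaling factor in image processing and a corrected sentence in the Procedure. No new scans are needed.

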### Results measures

Each patient will fill in a headache diary during the 4 consecutive weeks immediately before the trial (baseline period), and during the 4 weeks following it (see figure 1). The diaries will be complemented with information on 4 additional weeks, from week 21 to week 24 after randomization (the follow-up period) Headache severity should be recorded in the diaries on a 3-point scale, by which 1 represents the presence of mild pain, 2 represents moderate pain and 3, severe pain (with incapacity to carry out everyday activities or necessity to remain in bed). The diary will also record the symptomatic and/or prophylactic medication taken, specifying the brand name and the number of doses. It should be clearly stated on the cover of the diary that the information contained within it is confidential. In addition, before starting the treatment, and also at 12 and 24 weeks after starting it, the patients will be requested to fill in a questionnaire with sociodemographic data and information concerning days off work because of headache; this will be compiled together with the Goldberg Anxiety-Depression Scale register and the results obtained from the Spanish version of the Headache Impact Test [36] and the SF-12 Health Survey (version 2). The purpose of this is to evaluate health-related aspects of the patient's quality of life [37]. The adverse effects of the techniques under study, and those of any rescue medication taken by the patient, will also be recorded. During the baseline evaluation, the patient will be asked to provide an anamnesis of the characteristics of the headache, in accordance with the recommendations of the International Headache Society, in order to classify the type of headache and to assess the term of the pain. Following this, an anamnesis and examination will be performed in accordance with the norms of traditional Chinese medicine.

**Figure 1 F1:**
[figure not shown]
Trial work plan.

#### Primary outcome measure

▪ The difference in the number of days with migraine (DWM) between the baseline period and the period spanning weeks 9–12 (DWM1).

#### Evaluation of treatment credibility

Patients in Groups A and B will be asked, after the fourth treatment session, four items to be assessed on a continuous analogue visual scale from 0 to 10 (0 = totally disagree; 10 = totally agree): (1) Do you believe this treatment will reduce the pain you are suffering?; (2) Does the treatment seem to be a logical one?; (3) Would you recommend this treatment to a friend or relative with the same problem?; (4) Do you believe this treatment could be applicable to treat other problems? [40,41]

#### Sociodemographic variables

The following sociodemographic variables will be ascertained: date of birth, sex, marital status, level of education and race.

#### Variables related to the severity of the problem, occupational aspects and an estimation of direct tangible costs

Duration, in years, of the headache, its frequency, the duration of each attack and the degree of incapacity produced by the migraine.

Health utility will be measured in quality-adjusted life years gained by each patient, calculating the area under the curve of the SF-12 at 12 weeks after the start of treatment [42]. To estimate the costs of the different treatments, a map of activities will be created, and we will measure the costs that distinguish them (acupuncture, conventional treatment). The activities will be evaluated using an Activity Based Costing approach, according to which each activity consumes resources (inputs) – personal, materials and pharmaceutical – in order to produce results (outputs). These activities will be assessed one by one. The cost of each therapeutic treatment is defined as the sum of the costs of each of the activities that make it up. Thus we shall obtain a more accurate view of the cost variation produced by each treatment with respect to every other one, and will be able to study its impact on the following subprocess, as well as to make use of this information in future studies. The cost components of the activities addressed and the criteria applied to evaluate them in financial terms are as follows:

1. **Personal**. The consumption of human resources involved in carrying out the different activities. This evaluation includes the cost per hour of each category of professional staff. The cost is estimated taking into account the data provided by the Andalusia Public Health Service (SSPA), and includes both the explicit cost (wages and salaries paid) and the implicit cost (time travelling to and from the clinic, the environmental cost of this travelling, etc.).

2. **Occupational**. We will record the number of days off work, or incapacitated for the performance of routine tasks.

3. **Materials**. This includes the consumption of materials required for carrying out each activity. Each such material cost will be evaluated in accordance with the price recorded in the corresponding catalogue of the supplies department/service at the hospital or health district in question.

4. **Pharmaceuticals**. We shall consider the costs of the different pharmaceutical products (quantity and unit of measurement), evaluated in accordance with the normal price for sale to laboratories.

5. **Opportunity cost**. This will include the sum of the outputs of the potential activities that are not carried out as the result of applying the treatment, when an alternative might be used, and will include the potential financial cost of the resources employed.

On the basis of the ABC approach, the resources imputed to each patient can be applied, within a multidisciplinary table based on a modular matrix to act in the manner of a 'meter' for each patient, to the analysis model and thus we obtain the SF-12 curve showing the variation in the patient's quality of life and the potential cost savings for the public healthcare system, together with the increased years of life attained for each patient.

#### Characteristic diagnostic variables according to traditional Chinese medicine

The acupuncture physicians participating in the trial will be required to record the information needed to make a diagnosis according to traditional Chinese medicine, including the following factors: (1) the location of the headache; (2) the meridian or meridians most likely to be involved; (3) internal factors such as Blood, Qi, Yin, Yang, etc.; (4) external pathogens such as Wind, Phlegm, Cold, etc.; (5) the internal organs affected; (6) the state of internal body functions such as Stagnation, Excess, or Deficiency.

